# Safety, Quality, and Acceptability of Contraceptive Subdermal Implant Provision by Community Health Extension Workers Versus Nurses and Midwives in Nigeria: Protocol for a Quasi-Experimental, Noninferiority Study

**DOI:** 10.2196/resprot.8721

**Published:** 2018-03-02

**Keywords:** drug implants, contraceptive prevalence, contraception, delivery of health care, family planning services, task shifting, Nigeria, community health workers, long-acting reversible contraception

## Abstract

**Background:**

As part of its Family Planning 2020 commitment, the Nigerian government is aiming for a contraceptive prevalence rate of 36% by 2018, and in 2014, approved a policy to allow community health extension workers (CHEWs), in addition to doctors, nurses, and midwives, to provide contraceptive subdermal implants. There is a lack of rigorous evidence on the safety of long-acting reversible contraceptive provision, such as implants, among lower cadres of health providers.

**Objective:**

This study aimed to compare implant provision by CHEWs versus nurses and midwives up to 14 days post insertion.

**Methods:**

The quasi-experimental, noninferiority study will take place in public sector facilities in Kaduna and Ondo States. In each state, we will select 60 facilities, and from these, we will select a total of 30 nurses and midwives and 30 CHEWs to participate. Selected providers will be trained to provide implant services. Once trained, providers will recruit a minimum of 8125 women aged between 18 and 49 years who request and are eligible for an implant, following comprehensive family planning counseling. During implant insertion, providers will record data about the process and any adverse events, and 14 days post insertion, providers will ask 4410 clients about adverse events arising from the implant. Supervisors will observe 792 implant insertions to assess service provision quality and ask clients about their satisfaction with the procedure. We will conclude noninferiority if the CI for the difference in the proportion of adverse events between CHEWs and nurses and midwives on the day of insertion or 14 days post insertion lies to the right of −2%.

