## Methods

### Study Design, Aim, and Objectives

The aim of this quasi-experimental, noninferiority study was to compare insertion of contraceptive implants (Implanon Classic and Jadelle; Table 1) by CHEWs with nurses and midwives in Nigeria.

The primary objective was to compare the safety of implant insertions by CHEWs with that of midwives and nurses on the day of the procedure and up to 14 days post insertion. Secondary objectives were to: (1) compare the quality of implant insertions by CHEWs with that of midwives and nurses; (2) compare client acceptability of implant insertions by CHEWs with that of midwives and nurses; and (3) assess acceptability of CHEW provision of implants to other health staff, clinic managers, and other key individuals such as policy makers.

For the purpose of this study, *safety* refers to implant insertions that minimize risk and harm to service users. We hypothesize that implant provision by CHEWs will be as safe and of high quality as provision by existing cadres of implant providers. Safety will be assessed by comparing rates of any adverse events (ie, those with a minor, moderate, or severe impact on a woman’s health) at the time of the procedure, or up to 14 days post insertion (Table 2). As the study is evaluating the provider and not the method itself, method-related adverse events such as hormone-related changes to menstruation pattern, headaches, and nausea will not be recorded; neither will the study examine the effectiveness of the method.

We define *quality* as the degree to which a provider or facility meets certain objective and subjective levels of health care delivery standards. The term covers all aspects of clinical service provision such as correct insertion, infection prevention, and disposal procedures, as well as pre- and post counseling and taking a client-centered approach. We define *acceptability* as the level of satisfaction experienced with the service received (in the case of the client) and the level of satisfaction with this aspect of the job (in the case of the provider).

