### Sample Size

#### Day of Insertion

Calculation of the number of participants required for the study is based on the primary outcome—the frequency of adverse events associated with insertion on the day of the procedure.

Studies documenting adverse events of implant insertion on the day of procedure have found them to be rare. For example, a randomized clinical trial of 2008 women found that 0.2% clients using Jadelle and 0.8% clients using Implanon Classic experienced complications at insertion [26].

To detect a difference in proportion of adverse events between the 2 study arms with a noninferiority limit of 0.5%, 80% power, and 95% confidence level on the day of implant insertion, we would require a sample size of 2462 in each study arm, giving a total sample size of 4924. To account for possible clustering, we will include a design effect of 1.5, increasing the sample size to 7386. To allow for incomplete records, we will increase this by 10% to a total sample size of 8125.

We estimate that each provider will receive approximately 10 insertion clients per month and that we may see a refusal rate of 20%. With a total of 120 providers, we expect to recruit 1200 clients per month. We would therefore need to recruit clients for approximately 7 months to achieve the required sample size for insertions.

#### By Day 14

We expect the number of adverse events observed by day 14 to be higher than that at day 0 as we may start to see infections. This reduces the required sample size needed to detect a difference between health care provider types. To detect a difference in proportion of adverse events between the 2 study arms with a noninferiority limit of 1%, 80% power, and 95% confidence level 14 days after implant insertion, we would require a sample size of 1225 in each study arm, giving a total sample size of 2450. To account for possible clustering, we will include a design effect of 1.5, making the size 3675. Assuming 20% loss to follow-up makes a total sample size of 4410. If we expect to recruit 1200 clients per month, it will take around 4 months to recruit the sample size we require.

All recruited clients will be asked to return to the inserting provider for a follow-up visit at 14 days post insertion until the sample size of 4410 is reached.

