### Data Analysis

Quantitative data will be analyzed using statistical software Stata, version 13 (Stata Corp. College Station, Texas). Complete case analysis will be conducted. For safety monitoring, complication rates by provider will be generated by the study manager in Abuja every 3 months, to identify any providers with unusually high complication rates. These data will be checked and response activities will be agreed at the 3 monthly technical advisory committee meetings to be held in Abuja, which will be attended by staff from MSION and MSI, and ministry of health officials.

Training and supervision data will be presented using descriptive statistics. Insertion adverse events of CHEWs will be compared for noninferiority against the complication rates of nurses and midwives. To assess the equivalence between the nurses and midwives and the CHEWs, the risk difference between the 2 provider types together with their 95% CI will be derived by use of a generalized estimating equation model to adjust for clustering. If the CI of the risk difference between the 2 groups falls within the predetermined margin of equivalence (–2% to 2%, which is equivalent of lower bound of one side 97.5% CI), the 2 types of service providers can be considered equivalent.

Sensitivity analysis will be designed to control for group assignment bias among the 2 states. They will be analyzed both separately and together to identify any differences in performance between CHEWs in the northern state compared with the southern state.

All quality and acceptability indicators will be weighted equally, except for those most critical (infection prevention, correct clinical technique, and advice on where to go in case of problems), which will be given a higher weight. The difference in mean quality and acceptability scores between CHEWs and midwives will be compared using a *t* test.

Analysis of qualitative data will be undertaken manually or using a qualitative analysis software such as N-Vivo. Quotations will be labeled by cadre of speaker, and a thematic analysis will be carried out. Transcripts will be read and reread. Extracts will be coded according to themes and subthemes that emerge from the data or that have been identified before the analysis such as those included in the in-depth interview guide. A selection of quotes representing different cadres and views will be used to write a report structured around these themes.

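### The primary time point and the noninferiority rule are not reconciled, and the wording leaves room for a day-0 pass to carry the overall safety claim

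*Protocol article*

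**What the plan says.** Five places in the Protocol article bear on this.

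- **Abstract, Methods.** This is the only sentence that says when noninferiority is concluded. The interval is for "the difference in the proportion of adverse events between CHEWs and nurses and midwives on the day of insertion or 14 days post insertion", and it must lie above −2%. It is one criterion with two time points joined by *or*.
- **Study Design, Aim, and Objectives.** The primary objective is safety "on the day of the procedure and up to 14 days post insertion". In the next paragraph, safety is measured by the rate of any adverse event "at the time of the procedure, or up to 14 days post insertion (Table 2"). Here *or* is attached to when an event occurs.
- **Sample Size.** Day of Insertion rests on "the primary outcome—the frequency of adverse events associated with insertion on the day of the procedure", with a "noninferiority limit of 0.5%, 80% power, and 95% confidence level on the day of implant insertion" and 2462 per arm. By Day 14 then sizes a second comparison with its own 1% limit and 1225 per arm. Return visits are requested only until 4410 clients are reached.
- **Data Analysis.** "If the CI of the risk difference between the 2 groups falls within the predetermined margin of equivalence", given as −2% to 2%, the cadres count as equivalent. No time point is named, and nothing says how two results would combine.
- **Table 2.** Expulsion, paresthesia, prolonged pain, scarring, and the three infection signs (redness or swelling, discharge, fever) are marked day 14 only. Hematoma, bleeding and other reactions are marked for both days.

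**The concern.** Four statements of the primary comparison do not agree: day 0 *or* day 14, day 0 *and* up to day 14, day 0 alone, and no time point at all. No analysis can satisfy them all, so this is a contradiction in the text and not a detail left to a fuller plan.

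What is at stake is the headline safety conclusion. If *or* is taken to mean that either time point suffices, the conclusion can rest on day 0. Several of the harms that a less experienced inserter might cause cannot appear in the day-0 result at all. Sample Size itself expects more events by day 14, because infections may begin to show. The day-0 comparison also has the lower expected event rate and the larger sample, so it is the easier one to pass at a common 2% margin.

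Results reports that data cleaning is complete and analysis is being finalized. An unresolved rule therefore leaves the choice of reading open until after the data are in hand.

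**Working it through.** **Inputs.** From Sample Size: 2462 and 1225 per arm before inflation, limits of 0.5% and 1%, 80% power. From the Abstract and Data Analysis: 2% margin and 95% CI (one-sided 2.5%). Assumed: a day-0 rate of 0.5%, the mid-point of the cited 0.2% and 0.8%, and a day-14 rate of 1%, back-calculated because none is stated. Effective n is taken as the pre-inflation n, as if the design effect and losses turn out as planned.

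**Reproducing the stated sizes.** n = (z₁₋α + z₀.₈)² × 2p(1−p)/m².

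- Day 0, one-sided 5%: (1.645 + 0.842)² × 0.00995/0.005² = 2461, against 2462 stated.
- Day 14, one-sided 5%: (1.645 + 0.842)² × 0.0198/0.01² = 1225, against 1225 stated.
- One-sided 2.5% gives 3124 and 1555, which do not match.

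The assumed rates therefore fit the plan's figures, but at a one-sided 5% level that the analysis does not use.

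**Chance of passing each criterion.** With difference d taken as CHEW minus nurse/midwife, P(pass) = Φ((m − d)/SE − 1.96), where SE = √[(p₁(1−p₁) + p₂(1−p₂))/n].

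*Day 0, no true difference, m = 2%.* SE = √(0.00995/2462) = 0.00201, and 0.02/0.00201 − 1.96 = 7.99, so P > 0.9999. It stays above 0.9999 at both ends of the cited range (0.2%: SE 0.00127; 0.8%: SE 0.00254). Even with CHEWs at 1.5% against 0.5%, SE = 0.00283 and 0.01/0.00283 − 1.96 = 1.57, so P is about 0.94.

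*Day 14, nurses and midwives at 1%, m = 2%.* The CHEW rates above 1% are illustrative.

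| CHEW rate by day 14 | Expected 95% CI of difference | Day 14 passes | Either suffices | Both required |
|---|---|---|---|---|
| 1% | −0.8% to 0.8% | 0.9987 | about 1.00 | 0.9987 |
| 3% | 0.9% to 3.1% | 0.025 | about 1.00 | 0.025 |
| 4% | 1.8% to 4.2% | 0.0002 | about 1.00 | 0.0002 |
| 5% | 2.7% to 5.3% | about 0 | about 1.00 | about 0 |

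For the 5% row, SE = √(0.0574/1225) = 0.00685 and (0.02 − 0.04)/0.00685 − 1.96 = −4.88. The last two columns hardly depend on independence: P(either) is at least the day-0 probability, and P(both) is at most the day-14 probability.

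**Joint power under the Sample Size limits, equal true rates, 95% CI.** Day 0: 0.005/0.00201 − 1.96 = 0.53, giving 0.701. Day 14: 0.01/0.00402 − 1.96 = 0.53, giving 0.701. Both: 0.701² = 0.49 if independent, and at most 0.70 under any dependence. At one-sided 5% the independent figure would be 0.80² = 0.64, so the fall from 0.64 to 0.49 comes from the level and not from requiring both.

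**The case against.** The strongest reply is that no passage says either time point suffices. The Abstract sentence may describe one outcome: any adverse event on day 0 or by day 14. The safety definition uses *or* in that sense, and the Abstract objective is a single window to 14 days. On that reading day-14 events count, and rates of 5% versus 1% would fail the 2% criterion. A third reading is that each time point has its own conclusion, so a day-0 pass makes no overall claim. Data Analysis contains no either/or rule.

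This stands as far as it goes: a reader might infer that the plan has adopted an either-suffices rule, and the document does not establish that. It does not remove the problem. If one cumulative outcome was meant, the primary-outcome sentence in Sample Size is wrong. The relevant size would also be the day-14 one, because follow-up is sought only until 4410 clients are reached and the analysis is complete-case.

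Two further inferences should be resisted.

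- That the false-conclusion rate rises from 2.5% to 1 − 0.975² = 4.9%. This needs the either reading, both true differences at the margin, and independence. Day-14 clients are a subset of day-0 clients, with the same providers, and positive correlation would lower the figure.
- That requiring both time points costs much power. At the 2% margin it does not. The 70% and 49% figures belong to the 0.5% and 1% limits and partly reflect the separate mismatch between one-sided 5% and 2.5%.

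**Conclusion.** The point holds as an unreconciled decision rule and primary time point across the Abstract, Study Design, Sample Size and Data Analysis. It does not hold as a finding that the plan has chosen an either/or rule.

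The wording permits a day-0 result to carry the overall safety claim, and nothing in the article rules that out. Under that reading, at the 2% margin and with no day-0 difference, noninferiority is concluded about 100% of the time whatever happens by day 14. This includes 5% versus 1%, where requiring both would conclude it about 0% of the time. At 3% versus 1%, where the excess equals the margin, the contrast is about 100% against 2.5%.

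These figures rest on the assumed base rates of 0.5% and 1%, the pre-inflation sample sizes, a normal approximation, and the difference taken as CHEW minus nurse/midwife. The day-14 excesses are illustrations, not predictions. The day-0 result is not sensitive to the base rate within the cited 0.2% to 0.8%.

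**What to change.** Choose one of two rules and state it once.

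1. **Two primary comparisons.** Replace *or* in the Abstract so that overall noninferiority is concluded only if the criterion is met both on day 0 and by day 14. No alpha split is needed, because both must pass.
2. **One primary outcome.** Define any adverse event from insertion through day 14 as primary, with day 0 secondary, and base the primary sample size on clients followed to day 14.

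Under either rule:

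- State the margin for each time point, since the article gives 0.5%, 1% and 2%.
- State the sign of the difference. For CHEW minus nurse/midwife, the upper 95% limit must lie below the margin; a lower limit above −2% would not bound excess harm.
- Align the objective, the primary-outcome sentence in Sample Size, and Data Analysis.
- Because analysis is under way, say in the report when the rule was settled and whether results were known.

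**Cost.** This is a change of wording and needs no new data. At the 2% margin, requiring both keeps about 99.9% power when rates are equal. If the 0.5% and 1% limits are the intended margins, joint power with a 95% CI is about 49% if independent and at most about 70%. It should be restated, noting that part of the shortfall comes from sizing at one-sided 5%.

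### The primary safety rule is stated in two incompatible ways and the sign of the risk difference is never defined; the Abstract's version, read in the order it names the groups, sets no limit on excess CHEW adverse events

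*Protocol article*

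**What the plan says.** The rule for the primary safety comparison appears in two places.

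- **Abstract, Methods.** Noninferiority is declared when the interval for the cadre difference in adverse events "on the day of insertion or 14 days post insertion lies to the right of" −2%. Only a lower limit is set. CHEWs are named first and nurses and midwives second, but the subtraction is not defined here or elsewhere in the article.
- **Data Analysis.** The 95% CI for the risk difference comes from a generalized estimating equation model. The two cadres are considered equivalent if that CI "falls within the predetermined margin of equivalence", given as −2% to 2%. A parenthesis adds "which is equivalent of lower bound of one side 97.5% CI".

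The outcome is a harm. Under Study Design, Aim, and Objectives: "Safety will be assessed by comparing rates of any adverse events". A higher CHEW proportion is therefore the unfavorable direction.

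**The concern.** For a harmful outcome with the difference taken as new cadre minus standard cadre, the limit that protects clients is the upper one. A rule that asks only for the CI to lie above −2% shows that CHEWs are not more than 2 points safer, and says nothing about how much less safe they may be. Moving the CI further to the right, toward more CHEW harm, can never make it fail.

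Data Analysis does not settle the matter. A two-limit rule is not the same as a lower bound alone, yet the parenthesis treats them as one. It also changes the conclusion from noninferiority to equivalence. Two analysts following the two passages could report opposite verdicts from the same data, on the primary objective of a study meant to inform task-sharing decisions in other countries.

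**Working it through.** **Inputs**
- Day 0 (Sample Size, Day of Insertion): 2462 per arm before clustering, design effect 1.5, total 7386, so 7386 / 2 = 3693 per arm, and 3693 / 1.5 = 2462 effective.
- Day 14 (Sample Size, By Day 14): 1225 per arm before clustering, total 3675 after the design effect, so about 1837 per arm, or 1225 effective.
- Nurse/midwife event rate: not stated for either time point. I assume 0.5% at day 0, the midpoint of the 0.2% (Jadelle) and 0.8% (Implanon Classic) quoted from the randomized trial of 2008 women, and 1% at day 14.

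**The plan's own figures first.** n per arm = (z_alpha + z_beta)² × 2p(1 − p) / margin², at one-sided 5% and 80% power, so (1.645 + 0.842)² ≈ 6.183.
- Day 0: 6.183 × 2 × 0.005 × 0.995 / 0.005² = 2461 (stated 2462).
- Day 14: 6.183 × 2 × 0.01 × 0.99 / 0.01² = 1225 (stated 1225).

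The assumed rates therefore agree with those figures.

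**The two limits compared.** Let d = CHEW minus nurse/midwife, pC and pN the two true proportions, and SE = √{[pN(1 − pN) + pC(1 − pC)] / n effective}.
- P(lower limit > −2%) = Φ((d + 0.02)/SE − 1.96)
- P(upper limit < +2%) = Φ((0.02 − d)/SE − 1.96)

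| True CHEW excess (points) | Day 0, lower limit > −2% | Day 0, upper limit < +2% | Day 14, lower limit > −2% | Day 14, upper limit < +2% |
|---|---|---|---|---|
| 0 | 1.000 | 1.000 | 0.999 | 0.999 |
| 1 | 1.000 | 0.942 | 1.000 | 0.531 |
| 2 | 1.000 | 0.025 | 1.000 | 0.025 |
| 3 | 1.000 | 0.000 | 1.000 | 0.0002 |
| 5, 10 or 20 | 1.000 | 0.000 | 1.000 | 0.000 |

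The two-limit rule in Data Analysis behaves almost exactly like the upper-limit columns. The largest gap is at day 14 with no excess: 0.997 against 0.999.

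**Worked example, day 0, 10.5% against 0.5%.** SE = √[(0.005 × 0.995 + 0.105 × 0.895) / 2462] = 0.0063. The expected 95% CI is 0.10 ± 1.96 × 0.0063, about +8.8% to +11.2%. It lies wholly to the right of −2% and passes the Abstract rule. It lies wholly outside −2% to 2% and fails the Data Analysis rule.

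**Range of the assumed rate.** With no true excess, the case in which the Abstract rule is hardest to pass among those considered, pN = 0.8% gives SE = √(2 × 0.008 × 0.992 / 2462) = 0.0025 and Φ(0.02/0.0025 − 1.96), still about 1.000. A rate of 0.2% gives a smaller SE and the same answer.

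**The other sign.** If the difference were nurse/midwife minus CHEW, a 10-point CHEW excess would give a CI of about −11.2% to −8.8%, which is not to the right of −2% and correctly fails. The whole result for the Abstract rule turns on a sign that the article does not give.

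**The case against.** The strongest reply has four parts.

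1. *The order is open.* "the CI for the difference in the proportion of adverse events between CHEWs and nurses and midwives" names two groups without saying which is subtracted. If nurse/midwife minus CHEW was meant, −2% is the protective bound. This stands: a wrong bound is not proven, only the plain reading. But CHEWs are named first throughout as the cadre under test, nothing states the reverse order, and a one-sided safety rule with an undefined sign needs correcting in any case.
2. *Data Analysis caps the harm.* This stands. A CI held within −2% to 2% limits excess CHEW events whichever way the difference is taken. A reader might infer that the Abstract sentence is the only decision rule and that the study would pass CHEWs however unsafe they were. The documents do not support that. The absence of any cap belongs to the Abstract rule and to the lower-bound parenthesis, on the CHEW-minus-nurse reading.
3. *The parenthesis is right on confidence level.* Each limit of a two-sided 95% CI is a one-sided 97.5% bound. True, but that does not make two limits equal to one, and the word lower inherits the undefined sign.
4. *The two-limit rule would in theory fail CHEWs for being too safe.* This has little force at these rates. With no CHEW events at all, the lower limit would be near −0.8% at day 0 (−0.005 − 1.96 × √(0.005 × 0.995 / 2462)) and near −1.6% at day 14 (−0.01 − 1.96 × √(0.01 × 0.99 / 1225)), both short of −2%.

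**Conclusion.** The concern holds in this form: the primary safety rule is stated twice, the statements are incompatible, and the sign of the risk difference is undefined. On the plain reading, CHEW minus nurse/midwife, the Abstract rule bounds the wrong end and is passed with probability about 1.000 at every true excess from 0 to 20 points at day 0, and 0.999 or higher at day 14. The Data Analysis rule passes a true 2-point excess only 2.5% of the time and a 3-point excess practically never.

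These figures rest on the assumed nurse/midwife rates (0.5% and 1%), the design effect of 1.5 and a normal approximation. Varying the day 0 rate over 0.2% to 0.8% does not change the Abstract-rule result. The documents do not show that the authors intended the wrong bound, nor that the study as a whole has no protection against CHEW harm. The point should still be corrected, because it decides what may be concluded on the primary objective.

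**What to change.** In the Abstract and in Data Analysis:

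- Define the risk difference as the CHEW proportion minus the nurse/midwife proportion.
- Conclude noninferiority only if the upper limit of the two-sided 95% CI (one-sided 97.5%) is below +2%, the margin that both passages already use.
- Replace the equivalence wording and the lower-bound parenthesis with this single rule.

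At +2% this costs only wording: no change to data, staff or sample size. At the planned size and the assumed rates, the chance of passing with no true excess is about 100% at day 0 and 99.9% at day 14. Because Results says data cleaning is complete and analysis is being finalized, the clarification should be dated and should state whether it was made before the comparison by cadre was seen.

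The study was sized on margins of 0.5% (day 0) and 1% (day 14), not 2%. That mismatch is a separate issue to reconcile, and the no-cost statement applies only to the 2% margin. At 0.5% with a one-sided 97.5% bound, (1.96 + 0.842)² × 2 × 0.005 × 0.995 / 0.005² gives about 3124 per arm before clustering, against 2462 planned.
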